#### Serious Adverse Event (SAE) reporting & Monitoring

A SAE will be reported to the Dutch Department for Human Research (Centrale Commissie Mensgebonden Onderzoek), Baxter and Braun within 24 hours.

Requirements for SAE reporting will be:

1. (Prolonged) Hospitalisation (difined as a longer stay in the hospital than normally expected caused by a postoperative complication)

2. (Re-)operation

3. Death

Once a year, data from each center will be monitored. In compliance with GCP guidelines, monitors will verify data collected on data collection forms against source documents. Source documents are defined as any original records or data related to the trial or to subject treatment or medical history. Source documents include: original hospital, clinical, and office charts, laboratory notes, subject diaries or evaluation checklists, pharmacy records, recorded data from automated instruments, transcriptions (certified to be accurate after verification), magnetic media, or x-rays.

### Ethics

Before centers could participate in this trial, approval was obtained from the local medical ethics committee (Medische Ethische Toetsings Commissie, Erasmus MC). Patients will be extensively informed about the research project and can only participate after giving informed consent. Patients will always be permitted to withdraw from the study without providing further reasons. This will have no consequences for further treatment. Data of these patients will be evaluated in the final analysis. This trial was registered at Clinical trial.gov under NCT00761475.

### History and current status

After Ethical approval was obtained the trial started including patients in the middle of 2009. Initially the intake of patients was rather slow. This was attributed to the the low number of participating hospitals, the continued increase of laparoscopy and endovascular treatment, and the inclusion criteria of BMI >30. After the publication of Seiler et al. the BMI inclusion criteria were lowered from 30 to 27 [35]. The BMI amendment and the inclusion of additional participating hospitals made it possible to include more patients per month. Currently the trial is in the final stage of the inclusion of patients. It is estimated that the last patients will be seen in the outpatient clinic in the beginning of 2015. Around this time the final results will be subjected to peer-review for publication.

## Discussion

Incisional hernia continues to be one of the most frequent complications after laparotomy. Up to this date no intervention strategy has led to a resolution to this problem. In high risk patients, with a risk for incisional hernia more than 30%, an alternative technique with lower incisional hernia incidence would be highly desirable.

In daily practice almost all midline laparotomies are closed with slowly absorbable running sutures. This technique seems ample for low risk patients. Despite the high incidence of incisional hernia, this technique is still used in high risk patients. These patients are known to have altered collagen synthesis in wound repair or increased abdominal wall stress, leading to insufficient repair of the midline after operation.

In incisional hernia surgery the use of prosthetic mesh has proven its effectiveness and safety. For this reason a RCT investigating the effectiveness and safety of augmenting the closure of the midline with prosthetic mesh in high risk patients is being conducted. A high level of evidence will be obtained due to the design of the study, as it was a randomized, double blind, powered, multicenter study.

## Conclusion

The PRIMA trial is a prospective international multicenter double blind randomized trial comparing primary suture closure of midline laparotomy to closure aided with a prosthetic mesh. This trial might provide the surgical society a technique to prevent incisional hernia in high risk patients.

## Endnote

^a^The initial inclusion criteria featured patients with a BMI of 30 or higher. However as stated before, a study was published during the enrolment of this trial demonstrating that patients with a BMI 27 or more could also be included [35]. We amended our protocol to lower our inclusions criteria for BMI, from 30 to 27.

## Appendix

**Criteria for defining a Surgical Site Infection (SSI)**[49]

*Superficial Incisional SSI*

Infection occurs within 30 days after the operation *and* infection involves only skin or subcutaneous tissue of the incision *and* at least *one* of the following:

1. Purulent drainage, with or without laboratory confirmation, from the superficial incision.

2. Organisms isolated from an aseptically obtained culture of fluid or tissue from the superficial incision.

3. At least one of the following signs or symptoms of infection: pain or tenderness, localized swelling, redness or heat *and* superficial incision is deliberately opened by surgeon, *unless* incision is culture-negative.

4. Diagnosis of superficial incisional SSI by the surgeon or attending physician.

5. Do not report the following conditions as SSI:

6. Stitch abscess (minimal inflammation and discharge confined to the points of suture penetration).

7. Incisional SSI that extends into the fascial and muscle layers (see deep incisional SSI).

## *Deep incisional SSI*

Infection occurs within 30 days after the operation if no implant is left in place or within 1 year if implant is in place and the infection appears to be related to the operation *and* infection involves deep soft tissue (e.g., fascial and muscle tissue) of the incision *and* at least *one* of the following:

1. Purulent drainage from the deep incision but not from the organ/space component of the surgical site.

2. A deep incision spontaneously dehisces or is deliberately opened by a surgeon when the patient has at least one of the following signs or symptoms: fever (>38°C), localized pain, or tenderness, unless site is culture negative.

3. An abscess or other evidence of infection involving the deep incision is found on direct examination, during re-operation, or by histopathologic or radiological examination.

4. Diagnosis of a deep incisional SSI by a surgeon or attending physician.

Notes:

1. Report infection that involves both superficial and deep incision sites as deep incisional SSI.

2. Report an organ/space SSI that drains through the incision as a deep incisional SSI.

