**Methods/design:**

The **PRI**mary **M**esh Closure of **A**bdominal Midline Wound (PRIMA) trial is a double-blinded international multicenter randomized controlled trial comparing running slowly absorbable suture closure with the same closure augmented with a sublay or onlay mesh. Primary endpoint will be incisional hernia incidence 2 years postoperatively. Secondary outcomes will be postoperative complications, pain, quality of life and cost effectiveness.

A total of 460 patients will be included in three arms of the study and randomized between running suture closure, onlay mesh closure or sublay mesh closure. Follow-up will be at 1, 3, 12 and 24 months with ultrasound imaging performed at 6 and 24 months to objectify the presence of incisional hernia. Patients, investigators and radiologists will be blinded throughout the whole follow up.

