### Objective

The objective of this study is to evaluate the effectiveness of incisional hernia prevention in patients after laparotomy for aortic aneurysm and in obese patients with a BMI of more than 27. A double blind randomized controlled trial will compare the commonly used technique of running suture to closure with the aid of a prosthetic mesh.

•The primary outcome measure will be incisional hernia occurrence 2 years postoperatively.

•Secondary outcome measures will cover relevant postoperative complications, post-operative pain and quality of life.

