#### Group A. Primary closure of the midline

The midline fascia will be closed in all three groups with a running slowly absorbable suture *(MonoPlus, USP 1, Needle HRT48, 150 cm loop, B.Braun Aesculap, Tuttlingen, Germany).* The ratio of suture length to wound length of 4:1 is recommended (but not measured). Subcutaneous tissue and skin are closed in a fashion preferred by the surgeon.

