### Mesh supported closure

#### Group B. Onlay mesh supported closure

First, the midline will be closed as indicated in group A.

The Optilene Mesh LP will be positioned on the primary closed midline fascia with an overlap of 3 cm at each side. The mesh will then be fixed with fibrin sealant (5 ml). The fibrin sealent will be applied on the entire surface of the mesh, and in one shot having permanent contact between the mesh and the tip of the joining piece. Immediately after application of the fibrin sealant, the mesh will be smoothed with the back of a forceps to get a good fixation of the mesh on the entire surface and especially on the suture line. If present, it is also possible to use spray fixation using the EASYSPRAY system, *Deutschland GmbH, Unterschließheim, Germany.* When laparotomy is larger then 25 cm use 2 applicators of Tissucol (10 ml). Subcutaneous tissue and skin are closed in a fashion preferred by the surgeon.

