#### Post-operative data

•Blood transfusion

•Postoperative ventilation and duration

•Postoperative ileus and duration

•Postoperative complications:

○ Surgical Site Infection, according to the guidelines proposed by Mangram in 1999 [48]. (Appendix)

○ Wound hematoma: accumulation of blood in the wound area, which warrants surgical exploration and intervention.

○ Seroma subcutaneously

○ Pulmonary infections

○ Ventilation problems

○ Re-intervention and difficulties caused by the mesh at re-entry

○ Re-admission and indication

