### Statistical analysis

Three comparisons will be made leading to pair-wise comparison at alpha = 0.017 (=0.05/3) according to Bonferroni’s correction for multiple testing. Assuming a 30% rate of incisional hernia in group A, and about 10% in both groups B and C, for a power of 90% comparing group A versus group B and C, 92 patients are required in group A and 164 in groups B and C. Allowing for some dropouts, 100 will be included in the control group and 180 in each experimental group.

It is expected that differences between groups B and C can only be demonstrated with a very large number. Therefore it was decided to set the objective to showing “non inferiority” for onlay (group C) versus sublay (group B). Setting the non-inferiority margin at 10%, the power to show non-inferiority regarding the incidence rate of incisional hernia will be greater than 80%.

For the comparison of both experimental groups with the control group, Kaplan-Meier curves will be constructed and the log-rank tests will be performed. These logrank tests will be done with stratification by center and operation indication.

For the comparison of both experimental groups B and C, the cumulative 2-years probability will be calculated with the one-sided 98.3% confidence interval for the difference. Analysis will be done according to the intention-to-treat principle in comparing group A with groups B and C. For the comparison of groups B and C a per-protocol analysis will be the primary analysis.

Comparison of VAS and QOL scales between groups will be done using Repeated Measures Anova (SAS PROC MIXED) with baseline value, age, gender, operation indication and center as covariates.

The following putative risk factors regarding incisional hernia (smoking, infection, diabetes, corticosteroids) will be evaluated using Cox-regression.

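### The deep and organ/space infection definition gives mesh patients a 1-year counting window and controls without another implant 30 days, which biases this secondary safety comparison against mesh

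*Protocol article*

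**What the plan says.** All references are to the protocol article.

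- **Outcome.** The Objective section states: "Secondary outcome measures will cover relevant postoperative complications, post-operative pain and quality of life". Under Post-operative data, the first complication listed is "Surgical Site Infection, according to the guidelines proposed by" a published source, with a pointer to the Appendix.
- **Windows.** For deep incisional SSI the Appendix counts infection "within 30 days after the operation if no implant is left in place or within 1 year if implant is in place", provided it appears related to the operation. The organ/space entry has the same condition. The superficial entry has a single window for everyone: "Infection occurs within 30 days after the operation".
- **Treatment.** "The midline fascia will be closed in all three groups with a running slowly absorbable suture"; group A receives nothing more at the fascia. In group B, "The Optilene Mesh LP will be positioned on the primary closed midline fascia with an overlap of 3 cm at each side". In group C the mesh is left behind the rectus muscle.
- **Data collection.** Outpatient follow-up records wound infection at 1, 3, 12 and 24 months on one schedule for all arms.
- **Second mention of infection.** Statistical analysis: "The following putative risk factors regarding incisional hernia (smoking, infection, diabetes, corticosteroids) will be evaluated using Cox-regression".

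The article sets no common SSI window for comparing arms.

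**The concern.** An implant-dependent window makes sense for surveillance, where the task is to attribute infections to a type of operation. It does not suit a comparison in which having the implant is the randomised exposure. Here the period over which an outcome can be counted is partly set by the allocated arm. A deep infection at month 3 that appears related to the operation is an event in groups B and C. The same infection is a non-event in a group A patient with no other implant.

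At stake is the safety side of the trial's question. The Discussion says the trial is to examine both effectiveness and safety of mesh augmentation. If SSI is tabulated by arm under the Appendix definition, part of any excess with mesh would come from the definition, and the table would not show how much.

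**Working it through.** **Which patients are affected**

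| Patient | Implant left in place | Window for deep and organ/space SSI |
|---|---|---|
| Group B or C, any indication | Mesh | 1 year |
| Group A, aneurysm repair with a graft | Graft, if it counts as an implant | 1 year |
| Group A, enrolled for BMI alone, no other implant | None | 30 days |

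The windows differ by a factor of 365/30 = 12.2. The inclusion criteria admit patients on BMI alone, so the last row is not empty. The article does not say whether an aortic graft counts as an implant and does not give the aneurysm share.

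**Size**

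The article states no SSI rate, so there is no figure of its own to reproduce, and the rates below are assumptions. Let the true risks be equal in all arms:

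- p = risk of deep or organ/space SSI by day 30 (assumed 3–5%)
- L = added operation-related risk from day 31 to day 365 (assumed 1–5%)
- g = share of controls with another implant (assumed 0 or 40%)

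Counted risk with mesh = p + L. Counted risk in controls = p + gL. Apparent risk ratio = (p + L)/(p + gL).

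| p | L | Mesh | Control, g = 0 | Ratio | Control, g = 0.4 | Ratio |
|---|---|---|---|---|---|---|
| 5% | 1% | 6% | 5% | 1.20 | 5.4% | 1.11 |
| 3% | 1% | 4% | 3% | 1.33 | 3.4% | 1.18 |
| 5% | 5% | 10% | 5% | 2.00 | 7% | 1.43 |
| 3% | 5% | 8% | 3% | 2.67 | 5% | 1.60 |

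These are the four corners of the assumed ranges, so they bound the ratio: 1.20–2.67 with g = 0 and 1.11–1.60 with g = 0.4. The true ratio is 1.0 throughout. The bias is p + L − (p + gL) = L(1 − g). It is never negative, and it vanishes only if L = 0 or g = 1.

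**Chance of a significant false excess**

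Take an intermediate case, p = 4%, L = 2%, g = 0, with the planned 100 controls and 180 + 180 = 360 mesh patients. Counted risks are 4% and 6% (ratio 1.50).

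- Pooled risk = (4 + 21.6)/460 = 5.57%
- Null standard error = √[0.0557 × 0.9443 × (1/100 + 1/360)] = 0.0259
- Standard error under the counted rates = √(0.04 × 0.96/100 + 0.06 × 0.94/360) = 0.0233
- Probability of a two-sided 5% result against mesh = Φ[(0.02 − 1.96 × 0.0259)/0.0233] = about 9%, where 2.5% is nominal in that direction

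With about four control events the normal approximation is rough. It does show that the main effect would be a distorted estimate; a significant false signal would be much less common.

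**After the fix**

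With one window for all, the counted risks are p versus p (30 days) or p + L versus p + L (1 year). The ratio is 1.0 for any p, L and g.

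**The case against.** The strongest case on the other side has five parts.

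- **It is a published case definition, and the article specifies no SSI analysis.** The Statistical analysis section gives no test or counting window for SSI, and tabulation of complications is commonly left to an analysis plan. This limits the point: the bias arises only if arms are compared under the definition as written. But the definition is one the article itself adopts for a stated secondary outcome, and nothing in it offers another window.
- **The data needed are largely collected in every arm.** This stands. It makes the problem easy to repair and lowers its severity.
- **The affected subset is narrow.** This also stands. Only late, operation-related, deep or organ/space infections in controls without another implant are lost. The requirement that a late infection be operation-related does not help, because a related late infection in such a control still cannot be counted.
- **Blinding.** A reader might infer that choosing the window forces assessors to learn the allocation, contrary to "Patients, investigators and radiologists will be blinded throughout the whole follow up". The document does not support that. Blinded assessors can record date, depth and signs, and the window can be applied later from the operative record.
- **Cox regression.** A reader might infer that an arm-dependent infection variable enters the hernia risk-factor model as if it were a baseline factor. The article says neither how infection is coded there nor that the Appendix definition is used, so this is not shown to be an error.

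**Conclusion.** The point holds at moderate severity. As written, the deep incisional and organ/space SSI definition gives mesh patients a longer counting window than controls without another implant. A mesh-versus-suture comparison on that definition is biased against mesh. The direction follows from the text alone.

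The size does not. The ratios above rest on assumed infection rates, on an assumed share of controls with an implant, and on equal true risk in all arms. If late operation-related deep infection is rare, or nearly all controls carry a graft that counts as an implant, the bias is small.

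A reader might go further and conclude that the whole infection comparison, or the trial's main result, is compromised. The document does not support that. Superficial SSI has one window in all arms, onlay and sublay patients both have mesh, and the primary endpoint is hernia at 2 years. Nor does the article name infection as the main harm of prophylactic mesh. It reports low infection rates in earlier studies and lists SSI as one item among the postoperative complications.

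**What to change.** For between-arm comparisons, remove the implant condition from the time window. Report deep incisional and organ/space SSI (a) within 30 days and (b) within 1 year, with the same window in groups A, B and C and the same requirement at each horizon that the infection be related to the operation. Apply the window at analysis, from recorded onset dates, so that outpatient assessors never need implant status. Keep the implant-dependent guideline definition as a supportive display, and state there whether an aortic graft counts as an implant. If SSI is used as a risk factor in the Cox regression, use the same common window.

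The cost is a change of wording and one extra table; treatment and visits do not change. One thing to confirm first is that the case report form holds the onset date and depth of each infection in every arm, since the article lists only wound infection by visit. Where it does not, the re-intervention and re-admission data and the serious adverse event reports can help to identify and date late deep and organ/space events.

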## *Organ/Space SSI*

Infection occurs within 30 days after the operation if no implant is left in place or within 1 year if implant is in place and the infection appears to be related to the operation *and* infection involves any part of the anatomy (e.g., organs or spaces), other than the incision, which was opened or manipulated during an operation *and* at least *one* of the following:

1. Purulent drainage from drain that is placed through a stab wound into the organ/space.

2. Organisms isolated from an aseptically obtained culture of fluid or tissue in the organ space.

3. An abscess or other evidence of infection involving the organ/space that is found on direct examination, during reoperation, or by histopathologic or radiologic examination.

4. Diagnosis of a deep organ/space SSI by a surgeon or attending physician.
